# Land-based versus aquatic resistance therapeutic exercises for older women with sarcopenic obesity: study protocol for a randomised controlled trial

**DOI:** 10.1186/1745-6215-14-296

**Published:** 2013-09-16

**Keywords:** Older people, Women, Sarcopenic obesity, Resistance exercises

## Abstract

**Background:**

Sarcopenic obesity is a health condition that combines excess adipose tissue and loss of muscle mass and strength. Sarcopenic obesity predisposes to more functional disabilities than obesity or sarcopenia alone. Progressive resistance exercises are recommended for older people as a potential treatment for sarcopenia and also for obesity. However, there is a lack of evidence indicating which programmes are best applied to older people, and no studies have investigated their effects on sarcopenic obese people. The aims of this protocol study are to investigate and compare the efficacy of land-based and aquatic resistance exercise programmes on improving muscle performance, functional capacity and quality of life of older women with sarcopenic obesity.

**Methods/Design:**

This is a protocol study for a parallel randomised controlled clinical trial. Eligible participants are older women (≥65 years) with a body mass index ≥30 kg/m ^2^ and hand grip strength ≤21 kg force. A total sample of 36 participants will be randomly allocated to one of the intervention groups in blocks of three: land-based, aquatic or control. Each intervention group will undergo 2-week sessions of a 10-week therapeutic exercise programme for strength, power and endurance training of the lower-limb muscles. Participants in the control group will not participate in any strengthening activity for lower limbs and will receive telephone calls once a week. Baseline and final evaluation of outcomes will encompass muscle performance of the lower limbs assessed by an isokinetic dynamometer; functional tests of usual walking speed, maximal walking speed (shuttle walking test), stair speed and the Short Physical Performance Battery; and health-related quality of life (Medical Outcomes Study Short Form Questionnaire – SF-36). Data collectors will be blinded to randomisation and will not be in touch with participants during the interventions.

**Discussion:**

This study is the first randomised controlled trial designed to evaluate resistance exercises in older patients with sarcopenic obesity. If our hypothesis proves correct, both intervention programmes will be effective, with the land-based exercises conferring better results in muscle performance.

**Trial registration:**

Registro Brasileiro de Ensaios Clínicos: RBR-9p5q67

## Background

Ageing is generally followed by physiological changes in body composition. Essentially, ageing involves a gradual loss of muscle mass, a process called sarcopenia, and an increased amount of adipose tissue, which may lead to obesity [1,2]. The process of sarcopenia also encompasses a worsening of muscle function, characterised by weakness or low physical performance [3]. Obesity prevalence among older people has reached levels comparable with young adults, especially among women [4]. In extreme cases, excess adipose tissue and muscle mass loss may be combined in a condition called sarcopenic obesity [5,6]. According to diagnostic criteria, the prevalence of sarcopenic obesity may reach 12% among individuals aged over 60 years [7,8]. Disability is more common among older people with sarcopenic obesity than those with either condition separately [9-11].

Progressive resistance exercises have been widely recommended to older people as a potential treatment for sarcopenia because they improve muscle performance and functional capacity [12-14]. There is a lack of evidence indicating which programmes are optimal for older people because resistance exercises are often applied with the same parameters as followed for young people [15,16]. In older people with obesity, these exercises can produce weight loss and muscle mass gains, improving body composition and preventing the worsening of sarcopenia [5,13,17]. In addition, resistance exercises may stem the pathological progression of sarcopenic obesity by reducing the levels of inflammatory cytokines [18-20].

Using an aquatic environment may be a suitable way for older people to exercise, especially for safety and comfort. For obese people, water-based exercises can minimise joint impacts and facilitate movements. Although aquatic-based exercises are common in clinical practice, there is little evidence of the effects of these exercises, especially because of methodological problems and small sample sizes in previous studies [21]. Some studies found significant benefits of aquatic exercises in muscle performance and functional capacity of older people, but they combined aerobic and resistance training programmes [22,23]. Those authors suggest that the strength gains associated with aquatic exercises are smaller than those resulting from land-based programmes.

Our research group has found evidence that resistance exercise programmes can improve muscle performance and reduce the inflammatory state of older people [24,25], but we were unable to find any studies that investigated the effects of progressive resistance exercises in sarcopenic obese people. Additionally, there is a lack of evidence about the effects of aquatic-based resistance training in general [15,21].

This study therefore seeks to answer the following questions: Do land-based and aquatic resistance exercise programmes improve muscle performance, functional capacity and quality of life of older women with sarcopenic obesity? Which of the two exercise programmes is more effective?

## Methods/Design

### Study design

This study is a randomised clinical trial with two intervention groups and a control group. This study was approved by the Ethics Research Committee of Federal University of Minas Gerais (Universidade Federal de Minas Gerais), Belo Horizonte, Brazil, under number ETIC 0172.0.203.000-11.

### Sample size

The effect size of the interventions was estimated at *f* = 0.20, based on previous studies of similar exercise programmes and the target population [15,26,27] and a pilot study conducted with 12 volunteers. The sample size was calculated assuming a mixed design of repeated-measures analysis of variance in the programme G* Power, version 3.1.2 [28], considering α = 0.05, β = 0.80, three groups and a correlation of 0.8 between the two repeated measures, with a resultant total of 30. Adding a possibility of 15% missing participants, the final sample size was calculated as 36, with 12 subjects per group. Figure 1 shows the flow diagram for participants in this study.

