## Discussion

To the best of our knowledge, this is the first randomised controlled trial designed to evaluate the benefit of resistance exercises for older people with sarcopenic obesity. Considering the obesity epidemic and sedentary habits of western populations in general, it is essential to find interventions that can address both problems. We chose to select only older women because of their greater longevity and higher risk of functional disabilities.

Providing assurance that rehabilitation techniques are really effective in an evidence-based way is important. To achieve this, we developed a study design using an appropriate power calculation to estimate the sample size. This clinical trial will provide substantial information about the effects of a common practice in the rehabilitation field. Exercise interventions are considered a nonpharmacologic and noninvasive technique that can improve functional capacity and prevent or reverse disabilities. If our hypothesis is correct, both intervention programmes will be effective, and the land-based intervention will produce better results for muscle performance and functional capacity. We will also investigate the effects on health-related quality of life.

Following the CONSORT Statement recommendations for randomised trials of nonpharmacologic treatments, we described our intervention protocols in detail, including all qualitative and quantitative components. Training and constant supervision will guarantee the programmes’ standardisation. In the interventions proposed in this protocol, it is not possible to blind participants or those administering the interventions. Researchers involved in outcomes assessment will thus be blinded to participant allocation and will have no contact with participants besides evaluation tests. Any harm or adverse events will be recorded and reported. Important to note is that it is completely feasible to carry out the exercise programmes proposed in this study in clinical settings. Our results will be analysed and published after discharge of the last randomised patient.

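### The sample size prints beta as 0.80, and the 80% power actually used covers only the three-group-by-time interaction, not the pairwise comparisons the trial asks about

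*Protocol article*

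**What the plan says.** The Sample size section of the protocol article starts from one overall effect: "The effect size of the interventions was estimated at *f* = 0.20". It names the method: "The sample size was calculated assuming a mixed design of repeated-measures analysis of variance in the programme G* Power, version 3.1.2". The remaining inputs are "considering α = 0.05, β = 0.80, three groups and a correlation of 0.8 between the two repeated measures", "with a resultant total of 30". An allowance of 15% for losses raises this to 36, or 12 per group. The section does not say which effect of the mixed design was powered, and gives no effect size for any pair of arms.

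The Background asks whether the two programmes improve outcomes and then "Which of the two exercise programmes is more effective". The Discussion says "we developed a study design using an appropriate power calculation to estimate the sample size" and, later in the same paragraph, gives the hypothesis that "both intervention programmes will be effective, and the land-based intervention will produce better results for muscle performance and functional capacity". The Statistical analysis section plans a mixed repeated-measures ANOVA with preplanned contrasts, an intention-to-treat analysis, 95% confidence intervals and significance at P<0.05.

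**The concern.** There are two linked problems.

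First, the printed beta is the complement of what was meant. As written, the trial accepts an 80% chance of missing the effect it was designed to find.

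Second, once beta is read as 0.20, the resulting power belongs to a 2-df test of whether the three groups change differently. A significant result there says only that some difference exists among the arms. The research questions and the hypothesis are comparisons of pairs: each programme with control, and land with aquatic. A reader who sees the calculation called appropriate, next to a hypothesis that land does better, may give a null land-versus-aquatic result more weight than 10 to 12 women per arm can support.

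**Working it through.** **Inputs from the Sample size section.** f = 0.20, alpha = 0.05, k = 3 groups, m = 2 measurements, correlation rho = 0.8, N = 30 before losses, 15% losses, 36 enrolled (12 per arm).

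**Step 1: reproduce N = 30.** For the within-between interaction in G*Power:

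lambda = f² × N × m / (1 − rho) = 0.04 × N × 2 / 0.2 = 0.4N, with df = 2 and N − 3.

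| N | lambda | df | Power |
|---|---|---|---|
| 8 | 3.2 | 2, 5 | 20.6% |
| 9 | 3.6 | 2, 6 | 24.5% |
| 27 | 10.8 | 2, 24 | 79.4% |
| 28 | 11.2 | 2, 25 | 81.2% |
| 30 | 12.0 | 2, 27 | 84.3% |

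Thirty is the first total divisible by three that exceeds 80%. Power of 20%, the literal reading, would need only 8 women (9 with equal arms). The other two effects of the design do not give 30 at 80% power: with equal arms the within effect needs 24 and the between effect 222. So the calculation used power 0.80 for the interaction. The inflation also reproduces: 30 / 0.85 = 35.3, which rounds up to 36 in three equal arms.

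**Step 2: turn the overall effect into pairwise differences.** With two measurements the interaction is a one-way comparison of change scores. On that scale the squared effect size is lambda / N = 0.4, so the squared deviations of the three mean changes sum to 3 × 0.4 = 1.2, in units of the squared SD of change. The split among arms is not in the document, so it is varied here as an assumption. Let the gains be 0 (control), aL (aquatic) and L (land). Then

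(2/3) × L² × (1 − a + a²) = 1.2, so L² = 1.8 / (1 − a + a²).

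The land-versus-aquatic difference is (1 − a)L and the aquatic-versus-control difference is aL. Each is tested with a noncentral t, noncentrality = difference × √(n/2), two-sided 0.05, pooled error df of 27 (n = 10 per arm) or 33 (n = 12), no multiplicity adjustment.

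Worked case, a = 0.5: L² = 1.8 / 0.75 = 2.4; L = 1.549; difference = 0.775 SD of change. The SD of change is √(2 × 0.2) = 0.632 baseline SD, so the gap is 0.49 baseline SD. With n = 10, noncentrality = 0.775 × √5 = 1.732 and power = 38.6%.

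| Aquatic gain / land gain | Land v aquatic, N = 30 | N = 36 | Aquatic v control, N = 30 | N = 36 |
|---|---|---|---|---|
| 0.25 | 67% | 76% | 13% | 14% |
| 0.33 | 59% | 67% | 19% | 23% |
| 0.50 | 39% | 45% | 39% | 45% |
| 0.75 | 13% | 14% | 67% | 76% |
| 0.90 | 6% | 6% | 78% | 85% |
| 1.00 | no difference | no difference | 82% | 89% |

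**Step 3: can both contrasts reach 80%?** The expression 1 − a + a² is unchanged when a is replaced by 1 − a, so the two contrasts mirror each other around a = 0.5. For any a between 0 and 1, the weaker of the two has its highest power at a = 0.5: 38.6% with 30 analysed and 45.3% with 36. No ordering land > aquatic > control gives 80% for both.

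**The case against.** Four points deserve a fair hearing.

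- The beta is a notation slip, and both 30 and 36 are right for the interaction test. This stands: the sample size does not change. The printed design property is still wrong.
- Powering a three-arm trial on its interaction is common, and a condensed article may leave contrast-level power to fuller documents. This also stands, so the absence of contrast power is not in itself the finding. The finding is that the one power figure given is printed wrongly, is not tied to a named effect, and sits behind a general statement of adequacy that does not extend to the pairwise questions.
- A reader might infer that the article claims the calculation powers land superiority. It does not. The Discussion calls the calculation appropriate for estimating the sample size and states the hypothesis separately. There is no such claim to withdraw; the statement only needs its scope.
- A reader might also take 39% as a fixed ceiling on land-versus-aquatic power. It is not. It applies to 30 analysed and to aquatic achieving half the land gain; with 36 analysed it is 45%, and at one quarter of the land gain it is 67-76%. In that last case aquatic versus control has only 13-14%, so the hypothesis that both programmes work loses its support instead.

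The document nowhere says that a null result will be read as equality, and 95% confidence intervals are already planned.

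**Conclusion.** The concern holds within these limits. The printed beta of 0.80 is wrong; the calculation used power 0.80, and its achieved value is 84.3% at N = 30 for the group-by-time interaction.

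That figure does not extend to the comparison of the two programmes. Land versus aquatic has roughly 13-45% power across the scenarios of aquatic achieving half to three quarters of the land gain with 30 to 36 women analysed. Under every ordering land > aquatic > control, at least one of land versus aquatic and aquatic versus control has no more than 39% power (30 analysed) or 45% (36 analysed).

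These contrast figures rest on the document's own f = 0.20 and correlation 0.8, on an assumed split of the effect among arms, on two-sided 0.05, and on no multiplicity adjustment, which would lower them (39% becomes about 23% with Bonferroni over three pairs).

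**What to change.** - In Sample size, print power = 0.80 (beta = 0.20) and state that it refers to the omnibus group-by-time interaction at N = 30.
- In the Discussion, qualify the statement about an appropriate power calculation as applying to that test.
- Give the power of the planned contrasts as a scenario range with its assumptions: for land versus aquatic, 39-45% if aquatic achieves half the land gain and 13-14% at three quarters; for aquatic versus control, 39-45% and 67-76% in the same two cases (30 to 36 analysed).
- State that a non-significant land-versus-aquatic contrast, reported with its already planned 95% confidence interval, is not evidence of equal effect.

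The cost is wording. Enrolment and the planned analysis stay as they are. The downside is a less favourable stated power for the second research question.

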**Figure 1 F1:**
[figure not shown]
Flow diagram of the study protocol.

### Study population

Volunteers for this study will be recruited from the database of our research group on aging. The general inclusion criteria for all of the older people enrolled in this database are community-dwelling people aged 65 years or older. The exclusion criterion is to be bedridden. The professor in charge of the research group will make available the information about sociodemographic and anthropometric characteristics of the registered older people. We will then search for obese older women. The potential volunteers will be contacted by telephone and invited to participate in this research project.

Eligible participants are older women (≥65 years) with a body mass index ≥30 kg/m^2^[29] and hand grip strength ≤21 kg force [30].

Exclusion criteria are: physical, sensory or cognitive disabilities that prevent testing or exercising; inability to adapt to an aquatic environment; cardiovascular, articular or metabolic disease in the acute phase or with unbalanced clinical symptoms; urinary or faecal incontinence; contagious skin diseases, ulcers or open wounds; currently attending physical therapy treatment for lower limbs; and underwent lower-limb surgery or had a lower-limb fracture in the 12 months before enrolment.

### Primary outcomes

Muscle and functional performance are the primary outcomes of this study. Muscle performance of lower limbs will be assessed using an isokinetic dynamometer (Biodex System 3 Pro; Biodex Medical Systems Inc., Shirley, NY, USA) by measuring the strength and power of the hips and knees. The functional capacity of locomotion will be assessed through tests of usual walking speed, maximal walking speed, stair speed and the Short Physical Performance Battery.

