Locomotion on stairs will be tested on a flight of 10 stairs with a handrail. In the first test, volunteers will be instructed to climb the stairs in their usual way, going up and down at once. The second test is to climb the flight of stairs as quickly as possible, stopping at the top of the stairs. Each test is performed twice, and the best time is recorded to calculate the usual stair speed and maximum stair speed as the ratio between the height of the stairs and the time spent to accomplish the task [39].

To prevent potential fatigue, muscle performance tests will be conducted on a day after the interview and functional tests. For tests of knee flexors and extensors, the manufacturer’s protocols (Biodex System 3 Pro; Biodex Medical Systems Inc.) will be followed in the sitting position. For hip muscles (flexors/extensors and the abductor/adductor groups), the tests will be performed in a standing upright position, using a stabilising device specially built for this purpose [40]. The testing order of muscles will be randomised by drawing lots. For each muscle, two different tests will be conducted. First, a test of five maximum concentric repetitions at an angular speed of 60°/second will be conducted to calculate strength as the total work (Joules) and peak torque (Newton-meters). Next, a test of 15 repetitions at a speed of 180°/second for knee muscles and 120°/second for hip muscles will be performed to calculate power as the work done per unit time, expressed in Watts [41]. All measures will be normalised to body weight.

Data collectors will be blinded to the participants’ later randomisation into groups.

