### Statistical analysis

For data analysis, we will use the Statistical Package for the Social Sciences version 15.0 (SPSS Inc., Chicago, DE, USA). The baseline characteristics of the sample will be described in frequencies or measures of central tendency and dispersion. The effects of exercise programmes will be evaluated by intention-to treat analysis. The number needed to treat for the study outcomes will be calculated considering values of minimum clinically important difference as positive effects. Repeated-measures analysis of variance for mixed design and two factors will be conducted with preplanned contrasts for each group of outcomes. If necessary, correspondent nonparametric tests will be used. The results will be described as 95% confidence intervals and considered significant at *P*<0.05.

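### At least 23 unranked primary variables share one P<0.05 rule, so the error rate for the primary question is not held at 5%

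*Protocol article*

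**What the plan says.** The Primary outcomes section of the protocol article states: "Muscle and functional performance are the primary outcomes of this study". Muscle performance is to be assessed "by measuring the strength and power of the hips and knees". Functional performance covers usual walking speed, maximal walking speed, stair speed and the Short Physical Performance Battery. No variable is put ahead of another.

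The Procedures section shows what these domains contain. The dynamometer tests cover two knee groups ("For tests of knee flexors and extensors") and four hip groups ("For hip muscles (flexors/extensors and the abductor/adductor groups"). For each muscle, one test is used "to calculate strength as the total work (Joules) and peak torque (Newton-meters") and a second "to calculate power as the work done per unit time, expressed in Watts". Stair speed yields two values, usual and maximum.

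The Statistical analysis section plans a mixed-design repeated-measures analysis of variance with preplanned contrasts for each group of outcomes. It then says: "The results will be described as 95% confidence intervals and considered significant at" P<0.05. The Sample size section uses one effect size, f = 0.20, at alpha 0.05, without saying which variable it describes.

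**The concern.** A trial that names many primary variables needs a rule for what counts as success: one lead variable, an order of testing, a composite, a requirement that all succeed, or a divided alpha. The article gives none. It gives one threshold for the results in general. Read naturally, each primary variable is tested at 0.05, and any of them could support a statement that a programme improved muscle or functional performance. The chance of at least one such statement being false is then well above 5%, and the sample size does not allow for it.

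**Working it through.** **Plan's own figure first.** Inputs from Sample size: f = 0.20, alpha 0.05, three groups, two measures, correlation 0.8 between them. The stated beta of 0.80 is read as power. For the group-by-time interaction, lambda = N x f² x 2 / (1 - 0.8), with 2 and N - 3 degrees of freedom.

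- N = 27: power 79.4%. N = 28: 81.2%. Rounded up to equal groups, N = 30: lambda = 30 x 0.04 x 2 / 0.2 = 12, power 84.3%.
- Dropout: 30 / 0.85 = 35.3, rounded up to 36.

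Both stated totals, 30 and 36, reproduce. They are correct for one variable tested at 0.05.

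**Count of primary variables.**

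- Muscle groups: 2 knee + 4 hip = 6.
- Measures per group: total work, peak torque, power = 3. So 6 x 3 = 18.
- Functional: usual walking speed, maximal walking speed, usual stair speed, maximum stair speed, Short Physical Performance Battery = 5.
- Total: 18 + 5 = 23, counting one value per muscle group.

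**Chance of at least one significant three-group test, no true effect.** If independent: 1 - 0.95^23 = 69%. For correlated outcomes there is no simple formula, so it was simulated with 10 women per group and 23 equally correlated null variables. The article gives no correlations between outcomes; those below are assumptions.

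| Event under no true effect | r = 0 | r = 0.5 | r = 0.8 |
|---|---|---|---|
| Any three-group test with P<0.05 | 69% | about 48% | about 26% |
| Any contrast favouring a programme over control | about 65% | about 37% | about 20% |
| The same, with that variable's three-group test also significant | about 39% | about 23% | about 11% |

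Repeat runs differ by about one percentage point. The second and third rows count only results in the favourable direction, which is what an efficacy claim needs.

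**What full adjustment would cost.** Bonferroni over 23 gives 0.05 / 23 = 0.00217 per variable. Power at f = 0.20 is then 40% with 30 completers and 54% with 36; about 51 completers are needed for 80%. A later correction across the whole set would therefore not fit the stated sample size.

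**Two primary variables at 0.025 each.** Same formula at alpha 0.025: 75% with 30 completers (lambda 12), 81% with 33 (lambda 13.2), 85% with 36 (lambda 14.4).

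**The case against.** **Multiplicity may be in an analysis plan that is not shown.** This is fair for the details of the contrasts and for the bare absence of an adjustment. It does not cover the rest: the article itself fixes the unranked primary set, the single threshold and a sample size at undivided alpha.

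**The analysis wording could mean testing by domain.** The section speaks of groups of outcomes and does not literally say each variable is tested unadjusted. Variable-by-variable testing is an inference, though the natural one, because no composite or multivariate test is described. Even two domain tests at 0.05 would give 1 - 0.95² = 9.75% if independent.

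**The outcomes are correlated.** This stands. Total work and peak torque come from the same five repetitions, and a walking-speed task is part of the Short Physical Performance Battery. The independence figures are an upper end, not an estimate.

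**Stronger readings that the documents do not support.** A reader might infer that a false efficacy claim is more likely than not. Counting only results favouring a programme, that holds only when correlations are low. A reader might also infer that the whole hypothesis in the Discussion (both programmes work, land-based is better) could follow from any single chance result. It needs three favourable contrasts; even if these may come from different variables, chance alone produces all three in only about 2% of trials at r = 0.5. Nor does the article say that the legs are analysed separately, so a count of 41 variables (2 x 18 + 5) is speculative.

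**Conclusion.** The concern holds in this form: the article makes at least 23 variables primary without ranking them, judges results at P<0.05 with no adjustment stated, and sizes the trial for one test. The stated rule does not control the error rate for the primary question. Over assumed correlations from 0 to 0.8, the chance of at least one contrast falsely favouring a programme over control is about 65% down to 20%, or about 39% down to 11% if the three-group test must also be significant. Even the lowest of these is more than twice 5%. The size rests on variable-by-variable testing, equal correlations and 10 completers per group. The direction of the problem does not depend on the exact correlation. The sample size arithmetic itself is sound.

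**What to change.** Before any outcome data are examined by group, the investigators should name one primary variable in each domain. Which two is their choice. All other muscle and functional variables become secondary, reported with confidence intervals and without efficacy claims.

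Test each primary variable at 0.025: the three-group effect first, then the three pairwise contrasts, also at 0.025, only if that effect is significant. This keeps the overall error at 5% or less. Within a variable, if all three groups are equal, a false contrast requires a false three-group result (at most 2.5%). If exactly two groups are equal, only one true null contrast remains, tested at 2.5%. Two variables sum to at most 5%.

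The contrasts must stay at 0.025. If Holm is applied only to the two three-group tests and the contrasts are then read at 0.05, the comparison of land with aquatic leaks: when both programmes work equally well, a false difference between them appears in 8% to 10% of simulated trials. Holding each domain at 0.025 throughout brings this back to 5% or less.

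The change is to wording, not to measurements, but it has a power cost. Under the trial's own assumptions, power per primary variable is 75% with 30 completers (84% at 0.05), 81% with 33 and 85% with 36. With the planned 15% loss, 36 x 0.85 = 30.6 women remain, so power would fall below the 80% target. The sample size statement should say so, and should say which variable f = 0.20 refers to.
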